###### Missing data

3.7.1.1.1

General and generalised linear mixed models use maximum likelihood estimation which produces robust/unbiased estimates as they make implicit corrections for missing data, hence they are likely to retain more power if participants are lost to follow-up than traditional repeated-measures ANOVA/ANCOVA approaches which use “complete-case-analysis” approach that only includes cases with no missing data in the analysis. Maximum likelihood estimation (MLE) for incomplete longitudinal data (continuous or categorical) uses all available information, which means all participants will be included in the analysis regardless of whether they had complete responses for all occasions/timepoints or not. The MLE estimates are consistent if the assumption of data missingness is MAR and is more robust than using imputed values.

If more than 5% of the outcome data are missing, a sensitivity analysis will be conducted comparing fitted models in terms of estimates and corresponding standard errors using maximum likelihood estimation with and without considering different imputation techniques.

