#### Procedures

3.6.1

Data will be collected either by researchers via the phone, in-person, in paper-based surveys, or by Community Connectors during program operations. Study data will be collected and managed using REDCap electronic data capture tools hosted on a secure server at Bolton Clarke (68), which only researchers will have access by password. Table 2 outlines the different levels and the data collected, while Table 3 outlines the time points of data collection. If data collection causes distress to participants, interviewing will be immediately halted and existing escalation procedures will be followed, including referral back to the referring healthcare provider (community members), service responsible (volunteers), or external mental health services.

**Table 3 tab3:** Schedule of enrolment, interventions and assessments, per SPIRIT guidelines (50).

	Study period				
Timepoint:	Screening	Baseline	3-months	6-months	12-months
Enrolment					
Screening	X				
Informed consent	X				
Intervention					
*Connect Local* intervention					
Usual care (no intervention)					
Assessments					
Single-item measure of loneliness (69)	X				
UCLA – LS 3 (58).	X	X	X	X	X
Lubben Social Network Scale (LSNS-6) (70).	X				
5 item Geriatric Depression Scale (GDS 5) (61).	X	X	X	X	X
Demographic information		X			
UCLA-LS4 (71).		X	X	X	X
Lubben Social Network Scale (LSNS-18) (59)		X	X	X	X
Mini-Social Phobia Inventory (Mini-SPIN) (60).		X	X	X	X
Warwick-Edinburgh Mental Wellbeing Scale (WEMWBS) (63);		X	X	X	X
EQ-5D-5L (62);		X	X	X	X
Goal attainment (64).		X	X	X	X
Community service impact survey				X	X
Resource use questionnaire		X	X	X	X
Perceptions (acceptability), use and satisfaction with program			X		
Process data			X	X	X
Perspectives of staff in General practice and other referral agencies			X	X	X

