##### Individual level

3.6.2.1

This is the level at which individuals are impacted directly, including older community members, volunteers and health and social service providers.

For older community members, we will consider the primary outcome as a mean change in loneliness, from baseline at 3, 6 and 12 months for participants receiving the *Connect Local* program, when compared to the comparator group. This will be measured using UCLA-3 as informed by previous research that support the sample size calculations (58). At this stage, there is insufficient research data to calculate sample size when using UCLA-4 (57), however this tool has been recommended for use by community organisations by Australia’s national network, Ending Loneliness Together (71), therefore we will also utilise this tool to capture loneliness to ascertain whether it can be utilised with this cohort in future studies.

As outlined in Tables 2, 3, secondary outcomes, including social isolation, social anxiety, depressive symptoms, and improvement in quality of life and wellbeing, are a mean change from baseline at 3, 6 and 12 months for participants receiving the *Connect Local* program, when compared to the comparator. Achieved goals, as measured by the Goal Attainment scale (64), will also be gathered from the intervention group.

For community volunteers involved in the *Connect Local* program, as per Tables 2, 3, we will collect health-related quality of life and wellbeing measures at baseline, 3, 6 and 12 months.

Perceptions of the program will be collected from community members in the intervention group, volunteers and service providers involved in referred to the *Connect Local* program through interviews or focus groups at three months from participant baseline. Questions will invite participants to share their thoughts around the following aspects of the program: Relational (trust and trustworthiness, obligations and expectations, identity and identification), Cognitive (shared language, codes and narratives; shared values, attitudes and beliefs; and shared goals and purpose), and Structural (roles, rules, precedents and procedures).

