##### Quantitative data analysis

3.7.1.1

For all quantitative, repeated, continuous individual level variables (loneliness, social isolation, social anxiety, depressive symptoms, wellbeing, quality of life) the main research question will be whether the study intervention is effective at improving the outcome of interest compared with usual care. Modelling these data will focus on fitting linear mixed models using different covariance matrices such as: unstructured, an exchangeable-changeable and AR level-1 residual matrices, where the mean structure of all fitted models include a term for intervention group and a term for time and an interaction term for time and intervention. Non-linear outcomes will be fitted using Generalised Estimating Equations (GEE) analysis which requires that the missingness mechanism is Missing Completely At Random (MCAR). Alternatively, polynomials and/or piecewise linear functions will be utilised for modelling outcomes with non-linear growth trajectories if responses are Missing At Random (MAR). To ascertain whether the missing data is MCAR or MAR, we will utilise methods such as data inspection, applying domain knowledge and comparing summary statistics between cases with complete data and those with missing data to determine the missing data mechanism. An understanding of the mechanism will enable an appropriate statistical method to be chosen to handle the missing values in the data set.

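### The stated missing-data check compares methods that rest on MAR and never varies that assumption; add a delta-adjusted analysis of the UCLA-3 contrast by group

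*Protocol article*

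**What the plan says.** All references are to the protocol article.

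- **Primary outcome (Individual level, 3.6.2.1).** For older participants, "we will consider the primary outcome as a mean change in loneliness, from baseline at 3, 6 and 12 months", against the comparator group. "This will be measured using UCLA-3 as informed by previous research that support the sample size calculations". It is a self-report measure.
- **Mechanism (Quantitative data analysis, 3.7.1.1).** "To ascertain whether the missing data is MCAR or MAR, we will utilise methods such as data inspection, applying domain knowledge" and a comparison of summary statistics between complete and incomplete cases. The answer then guides the choice of method. MNAR is not mentioned.
- **Sensitivity analysis (Missing data, 3.7.1.1.1).** Mixed models fitted by maximum likelihood are described as robust and unbiased, with consistency tied to MAR. If more than 5% of outcome data are missing, estimates and standard errors are compared using "maximum likelihood estimation with and without considering different imputation techniques". The techniques are not named.
- **Expected loss (Sample size calculation, 3.6.2.3.1).** 15% attrition at 3 months.
- **Distress during data collection (Procedures, 3.6.1).** "If data collection causes distress to participants, interviewing will be immediately halted and existing escalation procedures will be followed". The same section allows several modes: "Data will be collected either by researchers via the phone, in-person, in paper-based surveys, or by Community Connectors during program operations".

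**The concern.** Comparing complete with incomplete cases can give evidence against MCAR. It cannot separate MAR from MNAR, because the two differ only in values that were not observed. A procedure with MCAR and MAR as its only outcomes will therefore settle on MAR at worst, whatever the truth.

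The planned sensitivity analysis does not fill the gap. Likelihood estimation and standard imputation built on similar variables both target the value that MAR implies. They are expected to agree if MAR holds and also if it fails, so agreement could be read as robustness when the doubtful assumption was left in place.

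MNAR loss is plausible here. People may withdraw because they have become lonelier or lower in mood than their earlier scores suggest, and some interviews may be stopped for distress. The groups are not randomised. Intervention participants have Connector contact and review, while comparators are recruited outside the area through a hospital and a care provider. Loss could differ between groups in either direction, and the primary contrast would then be biased without the stated check showing it.

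**Working it through.** **Inputs from Sample size calculation (3.6.2.3.1):** UCLA-3 reduction 0.85; standardised effect 0.37; 76 in the intervention group, raised to 88 for 15% attrition; 1:1 allocation. **From Missing data (3.7.1.1.1):** 5% trigger. **Assumed, because the article gives no figure:** the shift δ of unobserved scores from their MAR prediction, and the missing fraction m in each group.

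**1. The plan's own figures.** ((1.960 + 1.282)/0.37)² ≈ 76.8 with a two-sided one-sample or paired formula, close to the stated 76. Then 76 × 1.15 = 87.4, rounded up to 88, as stated. With 15% lost, 88 × 0.85 = 74.8, so about 75 per group remain. The argument below does not depend on how 76 was derived.

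**2. Will the check be run?** 15% exceeds 5%, so yes if attrition is as planned.

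**3. Scale.** Implied SD = 0.85/0.37 = 2.30 points. The article does not say whether this is the SD of scores or of changes.

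**4. Bias in the contrast.** If unobserved scores are worse than MAR predicts by δ, a group's mean is misstated by m × δ. The benefit is then overstated by

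bias = m(int) × δ(int) − m(comp) × δ(comp).

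| Missing, int / comp | Shift, int / comp | Bias (points) | Share of 0.85 |
|---|---|---|---|
| 15% / 15% | 0.85 / 0 | 0.15 × 0.85 = 0.13 | 15% |
| 15% / 15% | 2.30 / 0 | 0.15 × 2.30 = 0.34 | 41% |
| 15% / 15% | 0 / 0.85 | −0.13 | −15% |
| 15% / 15% | 1 / 1 | 0.15 − 0.15 = 0 | 0% |
| 15% / 5% | 1 / 1 | 0.15 − 0.05 = 0.10 | 12% |
| 5% / 5% | 1 / 0 | 0.05 × 1 = 0.05 | 6% |

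**5. A tipping point.** Suppose a difference of 0.85 is observed with 75 per group and SD 2.30. SE = 2.30 × √(2/75) = 0.375. The lower 95% limit is 0.85 − 1.96 × 0.375 = 0.115. With 15% missing and a shift in the intervention group only, the limit reaches zero at 0.115/0.15, or about 0.76 points. This holds the SE fixed and ignores the extra uncertainty from imputation.

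**6. What the planned check would show.** In every row of the table, likelihood estimation and imputation under a similar MAR model are expected to give nearly the same answer, and both would carry the same bias. The comparison therefore does not distinguish the zero row from the others.

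**The case against.** **The halting rule.** A reader might infer that it makes UCLA-3 missing because of its value at that visit. The article does not support this. It does not give the order of the scales, say whether answers given before a halt are kept, or say how often halts are expected. Table 3 lists UCLA-3 first among the instruments repeated at follow-up, though that does not establish the order. Distress could arise from another scale or from the perceptions interview, and paper surveys have no interviewer to stop. Distress predicted by earlier UCLA-3 scores would be compatible with MAR. The rule is one possible route to MNAR loss and no more.

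**Agreement by construction.** It is tempting to say that likelihood and imputation must agree. That holds, and only approximately, when they share variables and assumptions. The mean structure stated in 3.7.1.1 contains group, time and their interaction. Imputation that also used GDS-5, LSNS-18 or WEMWBS would rest on a different MAR assumption and could give a different answer. It would still not test MNAR. Unnamed techniques do not literally exclude an MNAR imputation, but none is stated.

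**Detail left to the analysis plan.** The MCAR-or-MAR sentence follows from the choice between GEE and other models. Naming techniques and shift ranges is usually left to an analysis plan, so their absence is no fault. What the article does fix is the pair of mechanisms and the type of sensitivity comparison, and the point concerns those.

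**Size.** The 15% and 41% figures put the whole shift in one group and treat the other as ignorable. The 15% is general attrition, not distress halts. The article reports no group difference in retention. This objection stands, and the figures are illustrations only.

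**Conclusion.** The point holds in limited form. The plan tries to settle the missingness mechanism from observed data, and its one sensitivity comparison leaves MAR untested for the primary effect at an attrition level that its own trigger treats as material.

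The size is unknown. Under the stated assumptions (15% missing, intervention-only shift, SD 2.30) the contrast moves by 0.13 points for a shift of 0.85, and by 0.34 points for 1 SD, which is taken as the upper end of the range. It moves by nothing when missingness and shift are equal in both groups, and the sign reverses if the comparators are the ones lost in a worse state. Bias needs a group difference in missingness or in shift. That is plausible in a non-randomised study but not shown.

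The article does not support reading 41% as an expected bias, or concluding that the primary result will be biased. This is a worthwhile, inexpensive improvement to the analysis, not an error that invalidates the design.

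**What to change.** 1. Keep the mixed model under MAR as the primary analysis of UCLA-3, and do not let a data-driven MCAR-or-MAR decision choose the method for that outcome.
2. Replace or supplement the imputation comparison with a delta-adjusted analysis. Shift imputed UCLA-3 scores in the intervention group, the comparator group and both, over 0 to 2.3 points, and report the shift at which the conclusion changes.
3. Record the reason for each missing visit (distress halt, withdrawal, death, move, unreachable) and tabulate it by group, so that readers can judge which shifts are credible.
4. Leave the halting rule as it is. As a low-cost safeguard, ask the UCLA-3 first at each follow-up and keep any items answered before a halt.

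The cost is one REDCap field, a set questionnaire order and some extra analysis. No visits or staff are added.

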##### Qualitative data analysis

3.7.1.2

For all qualitative individual, community and system level variables, interviews with participants will be audio-recorded, transcribed and then analysed utilising thematic analysis. Thematic analysis based on grounded theory involves finding repeated patterns of meaning within qualitative data (76) and will be facilitated with the use of qualitative management and analysis software such as NVivo (77). In addition, an interview summary will be created for each interview and circulated to the research team, facilitating the team’s ongoing knowledge of the data being collected. An inductive approach will be used within the project, which allows for themes and findings to emerge from the data, grounding the findings in the perspectives and experiences of participants. Finally, situational analyses will be used to supplement basic grounded theory with situation-centred approaches, enabling the consideration of all of the collective actors and the arena’s within which they engage to develop and fully articulate an ordered situational map (78).

###### Mixed method approach

3.7.1.2.1

Triangulation will be used to combine the qualitative and quantitative data using a deductive-simultaneous design (79) where the core component is quantitative, and the supplemental component is qualitative.

#### Outcome 2: health economic evaluation – program cost-effectiveness

3.7.2

The following accepted systematic approach to analyses of the SROI approach will be undertaken (47, 80).

The research team will identify and categorise the stakeholders, and the outcomes most relevant for each, and then apply the following tools of SROI (outlined below): consideration of deadweight, displacement, attribution and drop off. We will do this through discussion between team members undertaking evaluation and program implementation in relation to each of the outcomes considered in the SROI. See the Box 1 re: tools of SROI.

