### Individual and cost effectiveness outcomes

2.1

The outcomes related to the impact of the *Connect Local* intervention on older individuals and cost effectiveness will include a post-positivist ontological approach, where there is a single reality, imperfectly known (48, 49). Following on from this, our epistemological approach considers that we can only establish probable truths, as obtaining knowledge is subject to human error (48, 49). Axiomatically, we are considering that our intervention will make the community a better place by reducing loneliness, social isolation and/or depressive symptoms, leading to wellbeing, increased community activity/program use and reductions on health system use. The evaluation team aims to observe and measure the changes resulting from the *Connect Local* intervention, therefore position themselves outside the context of the intervention.

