### Community, health system and implementation outcomes

2.2

The outcomes related to the impact of the *Connect Local* intervention on the community, health system and the implementation of the program will be using a critical theory approach, where there are multiple subjective realities, influenced by power relations in society (48, 49). The knowledge is subjective, and co-constructed between individuals and groups (48, 49). The aim is to understand the relationships and these groups. The evaluation team is part of the implementation process, actively engaging and therefore position themselves inside the context of the intervention.

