##### Establishing impact

3.6.3.2

This stage will determine those aspects of change that would have happened anyway or are a result of other factors. Such aspects will be eliminated from consideration. Qualitative and quantitative data (surveys on loneliness, social connection, depressive symptoms, wellbeing and quality of life at baseline, 3, 6 and 12 months) will provide this evidence. Monetised outcomes will be discounted on the basis of what would have happened without the intervention (deadweight), what outcomes are displaced by the intervention (displacement), who else has contributed to the outcomes aside from the funder (attribution), and whether experience of the outcomes declines over time (drop off).

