**BOX 1 Tools used to calculate Social Return on Investment (SROI)**

**Tools of SROI**
Establishing impact (attribution, deadweight, displacement, drop-off):To minimise the risk of overclaiming the benefits it was necessary to account for deadweight, displacement, attribution, and attrition.*Deadweight:* responds to the question: ‘How much of the outcome would still be attained without the activity delivered?’We will use the quantitative data captured in the comparator group to ascertain this information, measured as a percentage, and then that percentage of the outcome will be deducted from the total quantity of the outcome.*Displacement* responds to the question: ‘Were there any activities with the same outcome displaced by the intervention being evaluated?’We will capture this information when collecting service information from participants involved in the program and comparing them to what was captured in the comparator group – using a percentage and deducted from the total outcomes.*Attribution* responds to the question; ‘Who else contributed to the attainment of the outcome?The research team will identify all relevant stakeholders and to assess how much of each outcome could be attributed to the delivery of Connecting Communities to Care with due circumspection. This will be calculated as a percentage.*Drop-off* responds to the question: ‘How much of the outcome is lost in the years post intervention?’To calculate the percentage of the outcome lost in the years after delivery of the intervention. It is calculated by deducting a fixed percentage from the remaining level of outcome at the end of each year. This will be calculated as a percentage.

*Calculating the SROI:*

The calculation of the SROI will consider the total value of the inputs in the program. The discounted, monetised value of benefits and outcomes will be divided by total investment (inputs) to estimate the SROI ratio.

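### Delivery staff help agree the SROI deductions although section 2.1 places the cost-effectiveness evaluators outside the intervention, and the two judgement-based deductions can decide whether the ratio exceeds 1

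*Protocol article*

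**What the plan says.** All references are to the protocol article.

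- **Independence.** Section 2.1 covers individual and cost-effectiveness outcomes. It says the evaluators observe and measure change and "therefore position themselves outside the context of the intervention". Section 2.2 takes the opposite stance, "actively engaging and therefore position themselves inside the context of the intervention", but for community, health system and implementation outcomes. It does not name cost-effectiveness.
- **Who applies the deductions.** Section 3.7.2 lists the SROI tools as "consideration of deadweight, displacement, attribution and drop off" and says of their application: "We will do this through discussion between team members undertaking evaluation and program implementation". This is done for each outcome, and the reader is referred to Box 1.
- **Where the percentages come from.** For deadweight, Box 1 says: "We will use the quantitative data captured in the comparator group to ascertain this information, measured as a percentage". For displacement it says: "We will capture this information when collecting service information from participants involved in the program", with comparison against the comparator group. Attribution is an assessment by the research team. Drop-off is a fixed yearly percentage, with no value or source given.
- **General evidence.** Section 3.6.3.2 says that qualitative data and the repeated surveys will provide the evidence for establishing impact, and it names all four deductions in the same paragraph.
- **The claim.** Section 3.2(ii) hypothesises a return greater than the investment, that is, a ratio above 1.

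**The concern.** Box 1 gives the purpose of the deductions as limiting overclaiming. They scale down the numerator of the ratio, so each percentage point bears directly on the hypothesis. The stated procedure brings the people who deliver the program into the discussion that applies this safeguard to their own program. Section 3.6.3 lists the lead care provider among the implementers. That sits badly with the outside position that section 2.1 claims for the same component.

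The exposure is greatest for attribution and drop-off, which Box 1 does not anchor to a named measurement. The Discussion says the SROI evaluation will help decision makers allocate resources and replicate the program, so a ratio that depends on agreed percentages would carry weight beyond the trial.

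**Working it through.** **Step 1: the four deductions side by side.**

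| Deduction | Source in Box 1 | Who applies it (3.7.2) |
|---|---|---|
| Deadweight | Comparator-group data | Evaluators and implementers, by discussion |
| Displacement | Participants' service data against the comparator | Same |
| Attribution | Research-team judgement | Same |
| Drop-off | Fixed percentage, no value or source | Same |

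The conflict over independence (2.1 against 3.7.2) covers all four rows. A possible conflict over source, data against discussion, arises only in the first two, and there section 3.7.2 can be read as applying the Box 1 data. In the last two rows Box 1 is itself judgement-based or unsourced. Section 3.6.3.2 supplies general evidence. However, the surveys it lists measure the outcomes rather than who else contributed to them, and they stop at 12 months, whereas drop-off concerns later years.

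**Step 2: can the judgement-based deductions decide the result?** The protocol gives no ratio, benefit value, investment or percentage, so there is no figure to reproduce. Every input below is an assumption. The deductions are taken as successive multipliers:

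SROI = G × (1 − deadweight) × (1 − displacement) × (1 − attribution) × Σ(1 − drop-off)^k, with k = 0, 1, … over the years counted.

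*Attribution, one year.* Take G = 2.0, deadweight 30% and displacement 10%. Before attribution the ratio is 2.0 × 0.70 × 0.90 = 1.26.

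| Attribution to others | 0% | 10% | 20% | 30% | 40% | 50% |
|---|---|---|---|---|---|---|
| SROI | 1.26 | 1.13 | 1.01 | 0.88 | 0.76 | 0.63 |

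Break-even: 1 − 1/1.26 = 20.6%.

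*Drop-off, three years.* Take G = 1.0 per year with the same deadweight and displacement. The yearly factor sums are 2.71, 2.19, 1.75 and 1.39 for drop-off of 10%, 30%, 50% and 70%.

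| Drop-off | 10% | 30% | 50% | 70% |
|---|---|---|---|---|
| Attribution 10% (0.567 × sum) | 1.54 | 1.24 | 0.99 | 0.79 |
| Attribution 30% (0.441 × sum) | 1.20 | 0.97 | 0.77 | 0.61 |

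In both illustrations deadweight and displacement stay fixed, as if taken from data, and the ratio still crosses 1.

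**Step 3: dependence on the starting ratio.** If R is the ratio before attribution, break-even attribution is 1 − 1/R. Suppose the ratio is 2.0 before displacement and attribution, and displacement is 5%. Then R = 2.0 × 0.95 = 1.90 and break-even is 1 − 1/1.90 = 47.4%. Moving attribution from 10% to 40% takes the ratio from 1.90 × 0.90 = 1.71 to 1.90 × 0.60 = 1.14, which does not cross 1. Whether judgement decides the conclusion therefore depends on how far above 1 the data-based part lands, and that is unknown.

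**The case against.** The strongest reply is that the sections fit together: 3.7.2 says who applies the tools and Box 1 says how. Section 3.7.2 refers to Box 1, and Box 1 states that the comparator percentage will be deducted. Section 2.1 is a statement of philosophical stance, not a rule about who attends a valuation meeting. Timing, sources and sensitivity ranges are often left to a fuller document.

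Much of this stands. A reader might infer that discussion can override a measured deadweight or displacement, but no text says so; what is missing is a sentence stating that the data prevail. A reader might also infer that implementers can set the size of their own return. The text does not support that either: the discussion is joint with evaluators, Box 1 gives attribution to the research team and asks for caution, and the declared aim is to avoid overclaiming. Nor is it right that attribution has no evidence behind it, since section 3.6.3.2 offers a general source.

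Two things survive. Section 2.1 expressly covers cost-effectiveness, so its claim to stand outside the intervention does not match 3.7.2. And the article does not merely stay silent on procedure: it states that delivery staff take part in applying the deductions. That is a stated choice open to bias, not detail lost in condensing.

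**Conclusion.** The point holds in limited form. Sections 2.1 and 3.7.2 disagree on whether the cost-effectiveness evaluation is kept separate from delivery, and implementers can influence the deductions, mainly through attribution and drop-off. Upward bias is a risk rather than a demonstrated effect.

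Its size cannot be derived from the protocol. Under the assumed multiplicative model (gross ratio 2.0, deadweight 30%, displacement 10%), about 21% attribution to others is enough to bring the ratio to 1. In the three-year case with 10% attribution, a drop-off of 50% gives 0.99. With a higher starting ratio the conclusion could survive a wide range of judgements.

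This concerns the economic component and leaves the primary loneliness outcome untouched. It merits correction because section 3.2(ii) is a stated hypothesis intended to inform policy.

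**What to change.** 1. Reconcile sections 2.1, 3.6.3.2, 3.7.2 and Box 1 on who stands outside delivery and on what evidence each deduction uses.
2. State in 3.7.2 that deadweight and displacement follow the data named in Box 1.
3. Have evaluators not involved in delivery set attribution and drop-off for each outcome, with the source recorded, before any between-group results are seen. Program staff supply information on other contributors but not the percentages.
4. Report the ratio over a pre-set range of attribution and drop-off, and say whether the conclusion on 3.2(ii) depends on them. There is no need to require a return above the investment across an arbitrary range: a 0% to 50% attribution range, for example, would demand a pre-attribution ratio above 1/0.50 = 2, a bar that nothing in the protocol supports.

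The cost is some rewording and one sensitivity table. The small downside is less direct use of implementers' local knowledge.
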